### Background of the Project including Preliminary Observations:

Diarrhoeal diseases are a leading cause of morbidity and mortality in children worldwide, with an estimated one billion cases and 500,000 deaths annually. While the majority of deaths due to diarrhoea occur in lower-income countries, infectious diarrhoea remains a significant problem in high-income countries. Aside from the immediate morbidity, potential long-term sequelae of diarrhoea in children in low-resource settings include malnutrition, growth faltering, and deficits in cognitive development.

While the cornerstone of diarrhoeal disease management in children is rehydration, a number of other management decisions, including the use of antibiotics and laboratory testing, may impact the course of disease. Overuse of antibiotics may cause side-effects and lead to increased antimicrobial resistance in the community. Underuse of antimicrobials for some bacterial and protozoal pathogens may lead to prolonged duration of illness and facilitate transmission. This can result in increased days of school or parental work missed, and among malnourished children in resource-poor settings, potential for growth faltering or death. Overuse of laboratory testing may have financial impact on both the patient and the healthcare system, and underuse may delay appropriate therapy or prevent recognition of outbreaks. Thus, accurate and cost-effective determination of diarrhoea etiology is important for proper case management in children and for public health.

#### Paucity of decision-making tools and guidelines for management of pediatric diarrhoea

Clinical prediction rules (CPRs) help clinicians interpret clinical information and can improve decision making.

 A recent systematic review showed that out of 137 studies of conditions for which clinical prediction rules have been developed for children only 2 were for diarrhoea, both of which are for the assessment of dehydration. Similarly, the majority of available guidelines for pediatric diarrhoea are focused on the route, timing, and choice of fluids for rehydration. A few studies in the past 30 years studied the use of clinical predictors to estimate the probability of a bacterial cause of diarrhoea. However, these studies were limited by low rates of pathogen identification, small sample sizes, use of a single study site, and suboptimal prediction performance.

Given the lack of guidelines and effective clinical predictors, decisions for use of antibiotics and laboratory testing are mostly empiric in nature, based on a number of “rules of thumb” for which evidence is scant. Unfortunately, physician judgment does very poorly to predict both need for antibiotics and correct type of testing. A recent study of children presenting to Kenyan hospitals with diarrhoea showed that reliance on dysentery as a proxy for *Shigella* infection led to the failure to diagnose Shigellosis in nearly 90% of cases. Better tools for decision making and evidence-based guidelines regarding use of antibiotics and laboratory testing in children with diarrhoea are clearly needed.

#### Decision-making for appropriate antibiotic use

The majority of decisions for use of antibiotics in diarrhoeal illnesses are made empirically. In lower- and middle-income countries (LMICs), due to cost constraints, etiological diagnosis is rarely made, and a large number (up to 70%) of patients with acute diarrhoea are prescribed antibiotics. However, in contrast to high resource settings, bacterial pathogens may be very common in low resource settings. In the multicenter Global Enteric Multicenter Study (GEMS) study, we found that detection of *Shigella* ranged from 16-78% of children with dysentery and 2-43% of children with watery diarrhoea. In both high and low resource settings, inappropriate use of antimicrobials leads to unnecessary toxicity for the individual, increased costs and an increase in antibiotic resistance in the community. Thus, methods for guiding appropriate use of antibiotics for pediatric diarrhoea in both high- and low-resource settings are urgently needed.

Clinical prediction rules (CPRs) are decision-making rubrics that help clinicians estimate the likelihood of a patient outcome. A number of prominent prediction scores have been widely adopted for clinical use. Examples include the CHADS2 score for stroke risk in patients with atrial fibrillation, the TIMI score for mortality in patients with NSTEMI, and the CURB-65 Score for mortality in community-acquired pneumonia. Clinical prediction rules integrated into clinical decision-making have the ability to direct clinicians towards more evidence-based behaviors, resulting in improved care and reduction of costs. CPRs can also reduce antimicrobial usage, as shown by the use of scores for strep pharyngitis, and linking CPRs with testing guidance may further reduce antimicrobial usage. Thus, clinical prediction rules have the potential to help healthcare workers worldwide address clinical uncertainty and provide improved care for children with diarrhoea.

We have recently use data from GEMS to derive a viral etiology prediction rule with an internal cross-validated area under the curve (AUC) of approximately 0.85. We used a post-test odds formulation method, which takes into account odds from multiple models or tests. First, using data from GEMS, we trained a logistic regression model with viral etiology as dependent variable using the five most predictive clinical variables as independent variables. We then trained models with the same viral etiology response using both local climate and recent clinical trends as independent variables. For each model, odds of viral etiology versus other known aetiologies are generated by estimating the conditional distribution of training predictions using kernel density estimates. The odds generated for each model are multiplied along with a pre-test odds to determine an overall odds of a viral etiology. We have now transferred the calculation of this prediction rule into a smart-phone application, called the Diarrhoea Etiology Prediction (DEP) algorithm. We have used TAC data from the VIDA (Vaccine Impact on Diarrhea in Africa) study to externally validate the DEP algorithm's ability to predict viral etiology of diarrhea. In this application, our objective is to determine the acceptability and use of the DEP among clinicians caring for children with diarrhea.

## Research Design and Methods

**Strategic Plan Overview:** This is a randomized crossover study, where clinicians will be randomized to periods where they will use a rehydration calculator application with or without the DEP. The crossover will include a washout period to reduce carryover effect. The study will be conducted over a 9-week period. We will use a random number generator to randomize clinicians to DEP or control arm for the first 4 weeks. After the first 4 weeks, there will be a 1-week washout period without decision support, after which each clinician will cross-over to the other arm for the next 4 weeks.

The DEP algorithm involves entry of clinical variables (age, bloody diarrhea, Breastfeeding, vomiting, mid-upper arm circumference- MUAC). The output provides the probability that the cause of the diarrhea is viral.

The DEP will be integrated as a feature into a Rehydration Calculator application that has previously been tested as part of two clinical studies in Bangladesh (icddr,b/ IEDCR; Khan AI et al, submitted 2019 and Haque et al. PLoS NTD 2017). The Rehydration Calculator with the DEP turned 'off' will serve as a control. The experimental arm of the study will have the DEP turned 'on'. The Rehydration Calculator is an electronic decision-support tool that provides recommendations for rehydration based on entry of age, gender, weight, and dehydration status. Given the outcome measures of this study, the Rehydration Calculator will be configured to not give antibiotic recommendations.

**Study Sites:** 4 Healthcare Facilities in Mali. ( CSRef CV, ASACOSAB1, CSRef CVI, ASACOYIR)

### Clinical setting:

The clinical approach will adhere to World Health Organization guidelines for the management of uncomplicated diarrhoeal disease in children with No, Some and Severe dehydration. These guidelines have previously been adapted to a digital format (e.g. Rehydration Calculator) and evaluated in a pilot and cluster randomized controlled trial (icddr,b/ IEDCR; Khan AI et al, submitted 2019 and Haque et al. PLoS NTD 2017); clinically relevant outcome measures in these studies were equivalent or improved with digital decision-support. The Rehydration Calculator version to be used in this study will include unchanged weights estimations and oral and intravenous (IV) fluid calculations; changes will include elimination of the antibiotic recommendations and replacement with the viral diarrhea probability. 15 physicians across 4 facilities will be enrolled.

## Operational Responsibilities:

All participant-based research, including consents, will be conducted in Mali. The DEP algorithm will be integrated as a feature into a Rehydration Calculator application that has previously been tested as part of two clinical studies in Bangladesh (icddr,b/ IEDCR; Khan AI et al, submitted 2019) and Haque et al. PLoS NTD 2017). The Rehydration Calculator with the DEP turned 'off' will serve as a control. The experimental arm of the study will have the DEP turned 'on'. The Rehydration Calculator is an electronic decision support tool that provides recommendations for rehydration based on entry of age, gender, weight, and dehydration status. Given the outcome measures of this study, the Rehydration Calculator will be configured to not give antibiotic recommendations.

## a. Detailed Research Methods

### c.i. Study design.

This is a randomized crossover study, where clinicians will be randomized to periods where they will use a rehydration calculator application with or without the DEP algorithm. The crossover will include a washout period to reduce carryover effect. The study will be conducted over a 9-week period. We will use a random number generator to randomize clinicians to DEP (use of the etiology calculator) or control arm (use of a previously-tested rehydration calculator) within site for the first 4 weeks. After the first 4 weeks, there will be 1-week washout period without decision support, after which each clinician will cross-over to the other arm for the next 4 weeks.

### c.ii. Study population and enrolment:

We will enrol both 1) diarrhea-treating clinicians, and 2) children presenting with acute diarrhea.

We will use the following inclusion/exclusion criteria for enrolling clinicians:

#### Inclusion criteria:

- Physician providing acute care for children with diarrhea at study hospitals
- Available to answer survey questionnaire

#### Exclusion criteria:

- Planning to leave the study site prior to completion of the research
- Inability to read

We will utilize the following inclusion/exclusion criteria when enrolling children:

#### Inclusion criteria:

- Age 2-59 months
- Less than 7 days of diarrheal symptoms from onset to presentation
- Three or more loose stools in the prior 24 hours
- Access to use of a cell phone

#### Exclusion criteria:

- No parent or primary caretaker available for consent
- Diarrhea lasting longer than 7 days
- Severe pneumonia, severe sepsis, meningitis, or other condition aside from gastroenteritis
- MUAC of  $\leq 11.5$  if  $>6$  months, or  $\leq 11.0$  if 2 to 6 months of age [we will exclude severely malnourished children because they would follow a different antibiotic protocol]

For the purpose of enrolment in our study, we will utilize the World Health Organization (WHO) definition for acute diarrhea, which is 3 or more loose stools per day in the last 24 hours. Subjects with chronic diarrhea (diarrhea lasting more than 7 days) will be excluded, as this study is focused on acute diarrhea.

**Staff Training:** Staff will receive intensive training regarding all study procedures prior to the study. A study coordinator will be trained to use the randomization block and distribute appropriate mobile phones to physicians and keep track of the devices. The study coordinator will also be in charge of administering questionnaires to physicians (details described in data collection section).

Staff will enrol patients according to the inclusion/exclusion criteria and they will receive training which includes an in-depth review of how to appropriately assess symptoms and MUAC. They will also be trained in calling patients for a post-visit follow up questionnaire.

Doctors will receive training on how to use the Rehydration Calculator and DEP application prior to the study. They will complete questionnaires before and after the study regarding previous use of clinical calculators, access to internet and willingness to use a new app that will help to predict etiology of diarrhea.

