### Outcome measures/variables:

The primary outcome is the proportion of children given antibiotic prescriptions, as assessed by hospital records. Secondary outcomes are the proportion of children with resolution of diarrheal symptoms at 10-days after enrollment, and clinician satisfaction towards use of the DEP, as assessed by pre- and post-study questionnaires

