#### Enrolment and consent of patients

Study staff will be situated in the intake areas and will identify children 2–59 months with diarrhoeal illness. Study staff will select consecutive subjects between 8am and 2pm on weekdays for enrolment on arrival to the Hospital. Potential participants' information (age and time of intake, etc) will be recorded in a screening log. Study staff and nurses will inform parents or primary caretakers (PPC) of patients who meet the inclusion/exclusion criteria about the study. If PPC is interested in the study, study staff will determine if the child is eligible and then provide more detailed information to the PPC's of eligible subjects. Detailed information will be provided in French and will include goals, risks, and benefits of the study. Once the PPC exhibits understanding, written consent will be obtained in the local language prior to enrolling the subject in the study. Illiterate PPC's will give consent by marking the consent form with their thumbprint or signature after a study staff member reads the consent form in French. Children without a PPC present will be excluded from the study. The last signature on the consent will be from the enrolling staff member.

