#### c.iii. Data collection

**Clinicians:** We will use a screening form (Appendix 3) and questionnaire (Pre- and post-Study) to collect quantitative (Appendix 4 & 5) data regarding clinician attitudes and experiences using the App and its role in diarrheal management. These questionnaires will be administered by study coordinators at 2 time points: 1) at the start of the study, and 2) at the end of the study. We will also use the App itself to collect data regarding physician usage.

**Children:** For each enrolled patient, study staff will collect:

- At enrolment, demographic and clinical variables
- At discharge, hospital outcome measures, including intravenous and oral fluids, and antibiotics, zinc administered
- At 10-days post-discharge, health outcomes including persistence of diarrheal and abdominal symptoms, returns to healthcare, and medication use since discharge, will be collected over a phone call.

**Instruments:** As mentioned, electronic tools that are compliant to the protections of PHI (Protected Health Information) will be used in this study. These include the Outbreak Responder software, which includes the DEP, and if needed, RedCap.

**Data Storage:** Data collected on Outbreak Responder software will be stored on a secure cloud-based server (server is physically based in Singapore; this is a HIPAA compliant server managed by Amazon Web Services).

Access to the server(s) will be restricted and the server management conforms to industry standard for health information.

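### The same study staff enrol children, collect discharge data and make the 10-day call, and nothing keeps the caller unaware of arm

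*Protocol*

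**What the plan says.** Four parts of the protocol bear on who collects the follow-up outcome and what they may know.

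- **Enrolment and calls.** The Staff Training paragraph in section c.ii says "Staff will enrol patients according to the inclusion/exclusion criteria", and then of the same group, "They will also be trained in calling patients for a post-visit follow up questionnaire". Enrolment and consent of patients places them: "Study staff will be situated in the intake areas and will identify children 2–59 months with diarrhoeal illness".
- **Data collection (c.iii).** The list opens "For each enrolled patient, study staff will collect" and covers three time points: enrolment, discharge (fluids, antibiotics, zinc) and the 10-day contact. At the last of these, "health outcomes including persistence of diarrheal and abdominal symptoms, returns to healthcare, and medication use since discharge, will be collected over a phone call".
- **Use of the data.** Outcome measures/variables states: "Secondary outcomes are the proportion of children with resolution of diarrheal symptoms at 10-days after enrollment". The primary outcome has a different source: "The primary outcome is the proportion of children given antibiotic prescriptions, as assessed by hospital records".
- **Allocation.** Section c.i randomises clinicians "within site for the first 4 weeks", followed by a washout week and crossover. The Clinical setting paragraph gives 15 physicians across 4 facilities. A study coordinator works the randomisation block and hands out and tracks the phones.

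No section describes blinding or masking of anyone.

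**The concern.** Physicians cannot be masked, because they see whether the DEP is on. The person who telephones the family ten days later can be. The plan names who calls but does not separate that task from the tasks that could reveal the arm.

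The hypothesis is that antibiotic use falls safely. Among the outcomes listed, symptom resolution is the one that speaks to the child's health. It is obtained by asking a caregiver over the phone, and some answers will be unclear, for example a child who is mostly better or who has had one loose stool. A caller who knows the arm may settle such answers according to expectation. A caller who favours the DEP could hide slower recovery in that arm, and a sceptical caller could create an apparent harm.

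**Working it through.** The protocol gives no figure on this point, so there is none to reproduce. The check traces roles and information, then bounds the possible effect.

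**1. Is it the same staff?** The Staff Training paragraph gives enrolment and calls to one group. Section c.iii assigns enrolment, discharge and 10-day data to study staff without distinction. The text does not say that the individual who enrolled a child phones that family, but nothing prevents it.

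**2. Could a caller know the arm?** The protocol does not say so. These features make it plausible:
- 15 physicians / 4 facilities = 3.75 per facility on average. Each stays in one arm for 4 weeks, so knowing the status of a few physicians gives the arm of all their patients.
- Allocation is within site, so both arms can run at a facility at the same time.
- Study staff determine physicians' eligibility and inform them about the study (Enrolment and consent of physicians), so they know who takes part.
- Study staff record antibiotics given at discharge. The DEP is meant to change that variable, so it is a further, imperfect clue.
- The same call asks about medication use since discharge, so even a caller unaware at the start may pick up a clue if that item comes first.

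The coordinator holds the allocation, but no section says that it is kept from other staff.

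**3. How large could the effect be?** Define:
- a = fraction of calls giving an ambiguous answer, taken as equal in both arms;
- k = share of calls made by someone who knows the arm;
- d = difference between arms in the share of ambiguous answers that such callers code as resolved (0 to 1).

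If unaware callers code alike in both arms, the spurious difference in the resolution proportion is a × k × d. With k = d = 1 it equals a, which is the maximum.

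The documents give none of these inputs. The values below are assumptions chosen to show the range.

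| k | d | a = 0.05 | a = 0.10 |
|---|---|---|---|
| 1 | 1 | 5 points (upper bound) | 10 points (upper bound) |
| 0.5 | 1 | 2.5 points | 5 points |
| 0.5 | 0.5 | 1.25 points | 2.5 points |
| 0 | any | 0 | 0 |

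In children, the planned number per arm is 15 clinicians × 12 = 180. Then a = 0.05 is 9 ambiguous answers per arm and a = 0.10 is 18. The upper bound needs every one of them coded one way in one arm and the opposite way in the other.

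**4. What is not touched?** The primary outcome is read from hospital records and does not use the call.

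**The case against.** The strongest reply is that caller awareness is never documented. These are study staff placed at intake, the coordinator is the one described as handling allocation and phones, and both arms use the same Rehydration Calculator with one feature on or off. Seeing a physician with a phone does not reveal the arm. This stands in part: awareness is an inference. The point that remains is that the plan does nothing to prevent it. Masking of outcome collection belongs in the protocol and is not normally left to an SAP.

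A reader might also infer four stronger things that the documents do not support.
- **That callers are facility employees working openly alongside physicians of known arm.** The text says study staff in intake areas and nothing about open allocation.
- **That symptom resolution is the only safety evidence.** Assessment of Safety requires all adverse events to be recorded, and serious events are captured until 10 days after discharge. Returns to healthcare are also asked about on the call.
- **That the call is an unstructured interview.** It uses a questionnaire. The wording of the resolution item is not in the text at hand and may already be fixed.
- **That the bias could match the planned 10-point primary effect (90% v 80%).** That sets a worst-case ceiling on an assumed ambiguity rate beside a different outcome with a different source. It says nothing about the likely bias.

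It is also fair that masking is not free. The protocol gives no staffing figures, and phone numbers are listed as protected health information under Individual privacy.

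**Conclusion.** The concern holds as a modest design weakness. The protocol gives enrolment, discharge data including antibiotics, and the follow-up call to the same study staff, and it has no measure to keep the caller unaware of arm. Within-site allocation among about four physicians per facility makes awareness plausible but not established.

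It affects one caregiver-reported secondary outcome and the other items asked on the call. The direction and size of any bias are unknown. The fraction of ambiguous answers is an upper bound on the spurious difference, and the true effect could be zero. The weakness is worth correcting because the outcome bears on the safety part of the hypothesis and the remedy is a reassignment of calls. It is no reason to doubt the primary comparison.

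**What to change.** Add to Staff Training and Data collection:

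- Each follow-up call is made by an existing trained staff member who neither enrolled the child nor collected its discharge data, from another facility where staffing allows.
- The caller works from a list holding only study ID, phone number and call date, with no physician, arm or treatment given.
- The resolution item is asked in fixed wording and its answer recorded before the medication-use items. If the questionnaire already does this, say so.

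The call date on that list needs one definition: Outcome measures/variables counts 10 days from enrolment and Data collection counts 10 days from discharge. The two should be reconciled.

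The cost is some call logistics, secure sharing of phone numbers between staff or facilities, and callers unfamiliar to the family, which might affect response. If one small team covers all four facilities, a change of facility may not help, and separation by individual child is the part to keep. Masking will not be complete, since a caregiver may mention treatment unprompted.
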